## Abstract

**Background:**

Knee osteoarthritis (OA) progression has been linked to increased peak external knee adduction moments (KAMs). Although some trials have attempted to reduce pain and improve function in OA by reducing KAMs with a wedged footwear insole intervention, KAM reduction has not been specifically controlled for in trial designs, potentially explaining the mixed results seen in the literature. Therefore, the primary purpose of this trial is to identify the effects of reduced KAMs on knee OA pain and function.

**Methods/design:**

Forty-six patients with radiographically confirmed diagnosis medial knee OA will be recruited for this 3 month randomized controlled trial. Recruitment will be from Alberta and surrounding areas. Eligibility criteria include being between the ages of 40 and 85 years, have knee OA primarily localized to the medial tibiofemoral compartment, based on the American College of Rheumatology diagnostic criteria and be classified as having a Kellgren-Lawrence grade of 1 to 3. Patients will visit the laboratory at baseline for testing that includes dual x-ray absorptiometry, biomechanical testing, and surveys (KOOS, PASE activity scale, UCLA activity scale, comfort visual analog scale). At baseline, patients will be randomized to either a wedged insole group to reduce KAMs, or a waitlist control group where no intervention is provided. The survey tests will be repeated at 3 months, and response to wedged insoles over 3 months will be evaluated.

**Discussion:**

This study represents the first step in systematically evaluating the effects of reduced KAMs on knee OA management by using a patient-specific wedged insole prescription procedure rather than providing the same insole to all patients. The results of this trial will provide indications as to whether reduced KAMs are an effective strategy for knee OA management, and whether a personalized approach to footwear insole prescription is warranted.

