Across 13 international clinical guidelines for management of knee OA, wedged insoles (i.e. insoles that elevate either the lateral or medial aspect of the foot) have been consistently recommended for disease management since they can influence KAMs [10]. On average across patients, laterally wedged insoles have been shown to reduce KAMs and reduce pain, while medially wedged insoles tend to increase KAMs; [4, 11] however, when considering subject specific reactions, 15-43% of patients, depending on the study, receiving either a medial or lateral wedge will experience KAM changes that are completely opposite to the group average result [12, 13]. This means that every year, thousands of North Americans with knee OA are being prescribed an incorrect wedge resulting in increased KAMs, and possibly accelerating and worsening their OA.

Interestingly, when reviewing past literature of major randomized trials for knee OA, no study has actually ensured that all patients experienced a reduction in KAMs in the experimental insole group, and this has likely had a large bias on study results [14, 15]. Thus, it is no surprise that a recent review has highlighted that large variability exists across studies in terms of the effectiveness of lateral wedge insoles [16]. Essentially, we still do not truly understand how or if wedged insoles and reduced KAMs can benefit patients with knee OA. Therefore a randomized trial is urgently needed that assigns wedged insoles on a personalized basis to ensure that KAMs are being reduced. Thus, the primary purpose of this study is to evaluate the effectiveness of a personalized wedged insole intervention on pain in patients with medial knee OA. Specifically, KAMs must be measured for each participant to ensure KAM reduction occurs with the intervention insole, rather than providing all patients with the exact same insole and assume a constant KAM effect as previous trials have done. This approach of ensuring KAM reduction has never been attempted before and so the results from this study will help evaluate the true clinical benefit of KAM reduction, and also the true effectiveness of wedged insoles. It is hypothesized that patients in the experimental group, where KAMs have been reduced using an individually prescribed wedged insole, will overall have greater improvements in pain and physical function over 3 months compared to the control group.

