### Eligibility, recruitment and evaluation for inclusion

The trial will have two parallel groups, where participants are randomly assigned to a waitlist control or experimental arm for a study duration of 3 months (Figure 1). Patients with painful radiographic medial knee osteoarthritis will be recruited from either the University of Calgary Sport Medicine Centre patient population (a Knee Osteoarthritis clinic is part of the services provided by this centre) or the Alberta Hip and Knee Arthroplasty clinics. Identified patients will be approached for inclusion into the study based on the inclusion/exclusion criteria described below. If recruitment is too slow to meet study timelines, advertisements of the project will be put into local newspapers and to other media. In these cases, a phone assessment of the volunteer will be undertaken for preliminary screening, and the individual will be invited for a detailed assessment by the study physician to determine their eligibility.

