Recently, it has been reported by a meta-analysis that future knee OA trials should utilize a flat insole as a control condition [16]. The motivation for this claim was based on the notion that this would control for placebo effects. However, recent evidence has suggested that even flat insoles can alter pressure distributions under the foot during gait [23], and thus it remains a possibility that KAMs could be influenced as well. Therefore, while flat insoles may control for placebo effects, they may not control for gait biomechanics, which is the primary concern of our trial. Consequently, the control condition for our study will be the participant’s own footwear, as this will control for gait biomechanics changes. Therefore, for biomechanical reasons, the trial will not be placebo controlled. In effort to ensure recruitment, compliance and participant retention in our control condition, we will utilize a waitlist control strategy, where we will indicate that a 3 month wait is required prior to providing an insole. After 3 months, we will provide control participants with access to a wedged insole, and continue to monitor them for safety.

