### Randomization

Following the baseline laboratory and survey testing, participants will be randomized into one of two study arms: (1) a KAM-reduction experimental group (KAM-R), or (2) a waitlist control group. In the KAM-R group, participants will be given either a medial or lateral wedge insole (whichever insole reduces KAMs more for each individual participant) to put inside their own shoe and use for 3 months. In the waitlist control group, participants will be asked to continue using their own shoes for a period of 3 months, and following this will be provided with access to a wedged insole (whichever reduces KAMs more based on baseline data collection).

Participants will be randomized using a multi-block-randomization procedure into either the KAM-R or waitlist control group. Specifically, a separate block sequence will be used for males and females to ensure an even sex distribution across groups. A block size of 6 will be used for each, and the sequence will be determined from a random number generator.

The one exception to this block randomization procedure is that if neither wedged insole produces a KAM reduction, the participant will be excluded from the main study altogether. This scenario will not be common, as most people do experience a large change in KAMs with one of the two wedged insole types, but this strategy will ensure that all participants in the KAM-R and waitlist control groups are all biomechanically suitable for a wedged insole intervention. Thus, neither group will contain biomechanical non-responders to wedged insoles.

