## Conclusions

In conclusion, this will be the first study to isolate the effects of reduced KAMs on symptom management for patients with mild to moderate medial knee OA over a follow-up period of 3 months. This study could therefore have strong clinical implications regarding personalized prescription of wedged insoles.

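### The randomized contrast is a KAM-selected wedge against no insole, so it cannot isolate the effect of reduced KAMs or show that personalized prescription is better than one wedge for all

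*Protocol article*

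**What the plan says.** The claims appear in four places.

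- Abstract, Discussion: "The results of this trial will provide indications as to whether reduced KAMs are an effective strategy for knee OA management", and also "whether a personalized approach to footwear insole prescription is warranted". The contrast drawn there is with giving every patient the same insole.
- Abstract, Background: the primary purpose is the effect of reduced KAMs on pain and function.
- Background: the results will "help evaluate the true clinical benefit of KAM reduction, and also the true effectiveness of wedged insoles". The same section also words the purpose more narrowly, as the effectiveness of a personalized wedged insole on pain.
- Conclusions: "this will be the first study to isolate the effects of reduced KAMs on symptom management".

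The design is stated in full.

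- Eligibility, recruitment and evaluation for inclusion: "The trial will have two parallel groups, where participants are randomly assigned to a waitlist control or experimental arm".
- Abstract, Methods/design, on the comparator: "or a waitlist control group where no intervention is provided".
- Randomization: KAM-R participants get whichever wedge lowers their KAM more. "In the waitlist control group, participants will be asked to continue using their own shoes for a period of 3 months" and are then offered a wedge chosen in the same way. Anyone whose KAM is lowered by neither wedge is excluded.
- Footwear insole interventions: a flat insole is considered and declined because it might itself alter KAM, and "for biomechanical reasons, the trial will not be placebo controlled".
- Blinding: participants in both arms know their allocation.
- Primary outcome measures: KOOS pain.

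Within group analyses adds a regression of pain change on KAM reduction in the KAM-R group. The main Discussion offers it as the answer to the placebo question. Between group analyses labels every arm comparison exploratory.

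**The concern.** Whether personalization is warranted is a question about personalized against uniform prescription, and the document itself names uniform prescription as the alternative. Isolating the effect of reduced KAMs requires a contrast in which KAM differs and other features of treatment do not. The trial has neither contrast under randomization.

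If KAM-R participants report less pain than controls, the same difference could arise from lowered KAM, from other mechanical or comfort effects of an insole, or from knowing one is treated rather than waiting. It could also arise if one lateral wedge for everyone worked just as well. The section on clinical relevance expects immediate implications for practice, and the Conclusions name personalized prescription. The overreach therefore falls on the claim most likely to be acted on, namely gait-laboratory selection of insoles.

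**Working it through.** **Step 1. Exposures by arm over the 3 months** (Randomization, Blinding, Footwear insole interventions).

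| | KAM-R | Waitlist |
|---|---|---|
| Given an insole | all | none |
| KAM lowered by assigned footwear | all, by selection | none, own shoes |
| Knows an insole was given | all | none |
| Insole assigned without regard to KAM | none | none |

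The first three rows are identical in pattern, so the arm difference on KOOS pain is one quantity that contains all three. The last row is empty: 0 of 46. Personalized minus uniform prescription has no data on one side, and recruiting more people to the same arms would not change that. The waitlist arm's later insoles do not help, because they are KAM-selected too.

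**Step 2. What the sample size was built for.** Inputs from Sample size calculation: difference 13.4, SD 15, two-sided α 0.05, power 80%.

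2 × (1.960 + 0.842)² × 15² / 13.4² = 2 × 7.849 × 225 / 179.56 = 19.7, so 20 per group. Then 40 × 1.15 = 46.

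The plan's figures reproduce. The plan describes the target as a 13.4-point change within each group. The paired formula also gives 19.7 if the SD is 15 at each visit with zero correlation. Neither personalization nor mechanism was sized.

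**Step 3. What the KAM-R regression can carry.** Take n = 20 in the arm, a simple correlation and the Fisher z approximation.

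- Correlation detectable with 80% power: tanh(2.802 / √17) = tanh(0.680) = 0.59.
- Power at r = 0.3: Φ(0.310 × 4.123 − 1.960) = Φ(−0.684) = 25%.
- Power at r = 0.5: Φ(0.549 × 4.123 − 1.960) = Φ(0.305) = 62%.
- With the two named covariates (adiposity, Kellgren-Lawrence grade), the detectable value is tanh(2.802 / √15) = 0.62.
- With all 23 recruited to the arm (46 / 2) and no covariates, it is tanh(2.802 / √20) = 0.56.

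The size of the KAM reduction is not randomized, so people whose KAM falls more may differ in other ways that predict pain change. Excluding those without a reduction also removes the zero end of the dose range.

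**Step 4. Illustration of the missing comparison.** Assume the two strategies give a different insole to 15% to 43% of people, borrowing the Background's range for opposite KAM responses. Assume each of those people differs by 13.4 points, with SD 15.

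- Mean contrast: 0.15 × 13.4 = 2.0 to 0.43 × 13.4 = 5.8 points.
- Per arm, 2 × 7.849 × 225 / contrast² (unrounded contrasts): about 875 down to 107. Twenty per arm gives 6% to 23% power.
- If the wrong wedge also worsened pain by 13.4 points, the contrast doubles to 4.0 to 11.5 points and needs 219 to 27 per arm.

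These are assumptions, not estimates. They show why simply adding a uniform-wedge arm at the present size is not the obvious remedy.

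**The case against.** Four points can be made for the plan.

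1. The Abstract promises only indications and calls the study a first step, and all arm comparisons are labelled exploratory. This stands: it would be wrong to say the plan commits to a firm conclusion on personalization. The verb isolate in the Conclusions carries no such qualification.
2. A reader might infer that KOOS pain can say nothing about either claim, or that any share of the arm difference from none to all could be due to KAM with no analysis touching the question. The documents do not support that. KAM reduction is measured as a percent change for each person, and the KAM-R regression relates it to pain change. The main Discussion argues that a slope away from zero would link pain change to KAM whether or not a placebo effect exists. That is fair as association. It does not remove confounding within the arm, it gives no estimate of the placebo effect, and it says nothing about personalized against uniform prescription.
3. The comparison with no insole is not uninformative about personalization. If a KAM-selected wedge did no better than nothing, the case for selecting wedges to relieve pain would weaken, subject to the plan's own warning about power. The asymmetry is that a positive result cannot show superiority over one wedge for all.
4. Declining a flat insole is a disclosed choice with a stated reason. It is not an error. Own shoes do hold control-arm mechanics constant. The price of the choice is that the arm contrast no longer isolates KAM, and the conclusions should reflect that price.

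**Conclusion.** The concern holds as a mismatch between the stated conclusions and the design. The randomized comparison supports one statement: the effect on self-reported KOOS pain of giving a KAM-selected wedge rather than no insole, in unblinded participants whose KAM falls with at least one wedge. The pain effect of personalization over uniform prescription is not estimable (0 of 46 on a non-personalized insole). The KAM effect is not separable from insole receipt in the arm contrast. The within-arm regression offers at most exploratory dose-response evidence, with adequate power only for correlations of roughly 0.56 to 0.62.

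The structural part rests on the arms as described and on no numerical assumption. The power figures assume 20 to 23 analysed in the KAM-R arm and a linear relation. An analysis plan not shown here could not supply the missing comparator, because the document deliberately declines an insole control. The narrower purpose in the Background, a personalized wedge against control on pain, already fits the design.

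**What to change.** - In the Abstract (Background and Discussion), the Conclusions, and the Background sentence on the true benefit of KAM reduction, limit the conclusion to the effect on KOOS pain of giving a KAM-selected wedged insole compared with no insole (waitlist).
- Delete the verb isolate, and delete the claim that the trial shows whether personalization is warranted.
- In the main Discussion, describe the regression slope as exploratory and associational, not as separating KAM effects from placebo effects.
- From the baseline walks of everyone tested, in both arms and including those excluded, report the proportion whose peak KAM is not reduced by the lateral wedge and the proportion for whom the medial wedge reduces it more. Label this as a biomechanical result, not a pain result.

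The cost is rewording and one descriptive table from walks already planned in all three footwear conditions. No arm, visit, outcome, test or sample size changes. The downside is a more modest headline claim.

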**Trial registration:**

NCT02067208.

**Electronic supplementary material:**

The online version of this article (doi:10.1186/1471-2474-15-405) contains supplementary material, which is available to authorized users.

## Background

Arthritis is one of the most prevalent musculoskeletal disorders, currently affecting 15% of people aged 15 years and older (~4.6 million Canadians), with an economic cost of $33 billion annually in Canada [1, 2]. The most common form is knee osteoarthritis (OA), affecting 16% of adults over the age of 45 [3]. It is characterized by degeneration of the knee joint cartilage, leading to severe pain, stiffness and swelling [4]. Commonly, symptoms will be severe enough to cause long-term disability [5, 6]. Currently, the gold standard treatment for severe OA is total joint arthroplasty (TJA) [7]. However, the majority of OA patients may be more suited for conservative management of OA, to either minimize symptoms in the short term, or ultimately prevent progression of OA to avoid the need for TJA.

Attention has been directed toward biomechanical interventions as they are generally low cost and relatively easy to implement. Biomechanically, cross-sectional and prospective studies have suggested that knee OA development and progression are related to increased peak external knee adduction moments (KAMs) during the single-leg support phase of walking [4–6]. This increased KAM is believed to induce large stress in the medial compartment of the knee, which, over time, contributes to cartilage degeneration, pain and ultimately OA [8]. Supporting this concept, increased KAMs have been positively correlated with higher Kellgren Lawrence grades, and cartilage loss over 12 months (KAM impulses), and negatively correlated with tibial cartilage thickness [5, 6, 9]. Thus, a focus for knee OA prevention and management has been to reduce these KAMs [4].

Across 13 international clinical guidelines for management of knee OA, wedged insoles (i.e. insoles that elevate either the lateral or medial aspect of the foot) have been consistently recommended for disease management since they can influence KAMs [10]. On average across patients, laterally wedged insoles have been shown to reduce KAMs and reduce pain, while medially wedged insoles tend to increase KAMs; [4, 11] however, when considering subject specific reactions, 15-43% of patients, depending on the study, receiving either a medial or lateral wedge will experience KAM changes that are completely opposite to the group average result [12, 13]. This means that every year, thousands of North Americans with knee OA are being prescribed an incorrect wedge resulting in increased KAMs, and possibly accelerating and worsening their OA.

Interestingly, when reviewing past literature of major randomized trials for knee OA, no study has actually ensured that all patients experienced a reduction in KAMs in the experimental insole group, and this has likely had a large bias on study results [14, 15]. Thus, it is no surprise that a recent review has highlighted that large variability exists across studies in terms of the effectiveness of lateral wedge insoles [16]. Essentially, we still do not truly understand how or if wedged insoles and reduced KAMs can benefit patients with knee OA. Therefore a randomized trial is urgently needed that assigns wedged insoles on a personalized basis to ensure that KAMs are being reduced. Thus, the primary purpose of this study is to evaluate the effectiveness of a personalized wedged insole intervention on pain in patients with medial knee OA. Specifically, KAMs must be measured for each participant to ensure KAM reduction occurs with the intervention insole, rather than providing all patients with the exact same insole and assume a constant KAM effect as previous trials have done. This approach of ensuring KAM reduction has never been attempted before and so the results from this study will help evaluate the true clinical benefit of KAM reduction, and also the true effectiveness of wedged insoles. It is hypothesized that patients in the experimental group, where KAMs have been reduced using an individually prescribed wedged insole, will overall have greater improvements in pain and physical function over 3 months compared to the control group.

## Methods

### Participant consent & ethical approval

Ethics approval for this study has been obtained from the University of Calgary Conjoint Health Research and Ethics Board (CHREB). In accordance with CHREB guidelines, written consent will be obtained from each individual prior to being enrolled in the study formally as a participant, and prior to any testing.

### Eligibility, recruitment and evaluation for inclusion

The trial will have two parallel groups, where participants are randomly assigned to a waitlist control or experimental arm for a study duration of 3 months (Figure 1). Patients with painful radiographic medial knee osteoarthritis will be recruited from either the University of Calgary Sport Medicine Centre patient population (a Knee Osteoarthritis clinic is part of the services provided by this centre) or the Alberta Hip and Knee Arthroplasty clinics. Identified patients will be approached for inclusion into the study based on the inclusion/exclusion criteria described below. If recruitment is too slow to meet study timelines, advertisements of the project will be put into local newspapers and to other media. In these cases, a phone assessment of the volunteer will be undertaken for preliminary screening, and the individual will be invited for a detailed assessment by the study physician to determine their eligibility.

**Figure 1 Fig1:**
[figure not shown]
**Flow of participants through the study.**

All patients considered eligible for the study must have physician-diagnosed knee OA primarily localized to the medial tibiofemoral compartment, based on the American College of Rheumatology clinical and radiographic diagnostic criteria [17]. Patients showing lateral compartment or patellofemoral OA in addition to medial knee OA will still be considered eligible as long as the medial compartment is the primary disease location and symptoms are attributed to the medial compartment. In addition, patients must be between the ages of 40–85 years of age, have no history of viscosupplement injections within the past 6 months, cortisone injection within the past 3 months, narcotic pain medication within the past 3 months, or use of other footwear insoles or unloader knee braces within the past 2 months, and must have a Kellgren-Lawrence grade (a measure of OA severity) of 1 to 3, as determined by a clinician, to avoid inclusion of end-stage OA patients that may be more appropriate for surgery [18]. Patients may continue to use anti-inflammatory medication or acetaminophen for mild pain management if needed. Those who meet the intrarticular injection criteria must also be willing to not undergo further treatment during the 3-month study. Patients must also present with a KOOS pain subscale score of 75 points or lower. This will help ensure that all participants have at least mildly painful knee OA. Any participant with recent (within 2 months) musculoskeletal or neuromuscular injury to the lower extremity that could bias pain assessments or gait analysis will not be considered eligible. For this reason, patients who typically use a cane will also be excluded.

